### 2.2. Information Source and Data Collection

Information on the patients who met the inclusion criteria will be extracted by the Tokushukai Information System Inc., while researchers will be blinded to statistical analyses. Figure 1 provides an overview of how variables will be collected.

Patient demographic data, including age, birth year and month, sex, postal code, and insurance type, were documented at the time of the issuance of medical record identification. In addition, body height, body weight, body mass index, body surface area, and date of measurement were recorded based on practical requirements. Moreover, the date of the last visit, the last date of survival confirmation, the date of death, and the diagnosis on medical receipt were automatically recorded as part of routine clinical practice. The above information can be extracted from a unified medical record system (e-Karte and Newtons2, Software Service, Inc., Osaka, Japan).

Treatment information, including inpatient and outpatient therapies, particularly chemotherapy regimens, can be retrieved from a shared chemotherapy protocol system (SSI srvApmDrop, Software Service, Inc., Tokyo, Japan). This system links the start and end date, the date of administration, the treatment interval, the number of treatment cycles, the dose of administration, the data of dose adjustment, and the performance status.

Data from the Japanese National Cancer Registry [19,20] are available for all hospitals, including the diagnosis (date, site, laterality, pathology, and differentiation), staging (clinical and pathological TNM classification [21]), date of the first visit, treatment details (surgery, endoscopic treatment, radiotherapy, chemotherapy, and endocrine therapy), and survival outcomes (last date of survival confirmation, date of death, and cause of death).

Patient, treatment, and cancer registry data are combined with anonymized identification and cleaned by Tokushukai Information System Inc. (Osaka, Japan). Patients with double cancer and/or diagnostic errors will be excluded from the study. Treatment history will be organized, and missing data will be supplemented by a direct check of medical records in cases of inconsistency or lack of information. Patients with unknown treatment history will be also excluded.

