### 2.5. Statistical Analysis

Basic statistics (absolute and relative frequencies for categorical variables; quartiles, maximum, minimum, and mean for continuous variables; and quartiles and relative frequencies for discrete variables) will be obtained to summarize the distribution of variables related to patient background factors, complications, other prognostic factors, and endpoints.

Kaplan–Meier curves will be obtained for each stratum consisting of patient background and prognostic factors for the occurrence of events associated with various endpoints (overall survival, time to treatment failure, recurrence-free survival, and adverse events). Several univariate logistic regression analyses will be performed, with the presence or absence of events in each stratum as the objective variable and the categorical value of each background or prognostic factor as the explanatory variable.

A hierarchical set of predictive models will be constructed by combining explanatory variables that are expected to contribute a single-layer or multi-layer proportional hazards model, which will be set up by incorporating each predictive model, and Cox multiple regression analysis will be performed. If proportional hazards are not acceptable, parametric hazard models such as the Cure–Weibull gamma-frailty model or the mixed Weibull gamma-frailty model will be applied for survival time analysis (including in combination with logistic regression models) [24]. Based on the likelihood (or partial likelihood in the case of Cox regression), the Akaike information criterion (AIC) and Bayesian information criterion (BIC) will be used to explore the optimal model (if the number of cases covered differs between models, the average AIC and BIC per case are used instead).

Regarding the estimated value of the regression coefficient of the explanatory variable included in the optimal model, if *p* value is <0.05, it will be judged as an important prognostic factor, and the 95% confidence interval of the hazard ratio regarding the magnitude of the contribution of that factor will be calculated.

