### Strengths and Weaknesses

This nationwide cohort study will include a large number of patients from community-based general hospitals only, not including cancer centers or academic institutions. The cohort will comprise a certain number of patients who are unable to participate in clinical trials owing to their age, poor performance status, or complications. Therefore, this study could provide more realistic clinical data with a lower rate of loss to follow-up.

Moreover, our study will simultaneously use demographic data and treatment details, as well as the National Cancer Registry, DPC, prescription, and laboratory test data. In particular, few large-scale databases include performance status and laboratory data, which would be major considerations regarding prognostic factors. In addition, by using the DPC data, detailed information on emergency hospitalization, length of hospital stay, concomitant complications, medical costs, and outcomes can be obtained, allowing for a review of the quality and cost-effectiveness of medical care. Prescription data would be useful for evaluating drug–drug interactions. Relative dose intensity can also be computed. Individual analyses using institutional or national databases are very common; however, to the best of the authors’ knowledge, this is the first large-scale cohort study that can simultaneously handle comprehensive RWD.

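### The p-value rule reads one coefficient per factor, so for a factor entered as three or more categories the verdict depends on the reference level

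*Protocol article*

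**What the plan says.** Section 2.5 first chooses a model: "the Akaike information criterion (AIC) and Bayesian information criterion (BIC) will be used to explore the optimal model". For variables in that model it then applies a cut-off to "Regarding the estimated value of the regression coefficient of the explanatory variable included in the optimal model". If the p "value is <0.05, it will be judged as an important prognostic factor", and for each such factor "the 95% confidence interval of the hazard ratio regarding the magnitude of the contribution of that factor will be calculated". Coefficient, p-value and hazard ratio are all in the singular. No joint test of a factor is named.

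The same section enters "the categorical value of each background or prognostic factor as the explanatory variable", but says so only for the univariate logistic regressions. Coding in the Cox model is not given.

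Section 2.2 lists several variables that naturally have more than two categories: performance status ("the dose of administration, the data of dose adjustment, and the performance status"), TNM stage, pathology, differentiation and insurance type. Strengths and Weaknesses singles out one of them: "few large-scale databases include performance status and laboratory data, which would be major considerations regarding prognostic factors".

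**The concern.** The rule works when a factor has exactly one coefficient, that is, when it is binary, continuous or scored as a linear trend. With k categories entered as indicators there are k-1 coefficients, and the rule does not say which p-value decides. The natural reading, that any one below 0.05 is enough, tests levels against a reference and not the factor. Changing the reference changes the set of contrasts and their standard errors, although the fitted model and its likelihood stay the same.

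Prognostic factors for overall survival are a stated aim (Introduction), pursued in separate sub-projects by cancer type. Two sub-projects that code the same factor differently could disagree about it for no clinical reason. A small reference group can hide a real effect. Pathology and insurance type are nominal, so a trend term is no way out for them.

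This arises within a single factor. It is separate from multiplicity across factors, endpoints or cancer types.

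**Working it through.** **Inputs from the article.** The cut-off is p < 0.05 (taken as two-sided, to match the 95% CI). The tested unit is a regression coefficient. AIC/BIC selection comes first (all section 2.5). Expected cohort sizes run from 350 to 10,000 (Table 3). Numbers of levels, level shares, effects and deaths are not given, so those below are assumptions.

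**Model.** The estimated log hazard of level j is approximately normal with variance 1/d_j, where d_j is the number of deaths in that level.
- Coefficient against reference r: z = (b_j - b_r) / sqrt(1/d_j + 1/d_r).
- Joint statistic: Q = sum of d_j (b_j - b_mean)^2, on k-1 df, where b_mean is the death-weighted mean. It does not involve r.
- AIC keeps the factor as a block if Q > 2(k-1).
- Each setting uses 400,000 draws.

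**Step 1: the stated cut-off.** With two levels there is one coefficient, and the null rejection rate is 5.0%. The cut-off behaves as expected in that case.

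**Step 2: why the reference matters.** Take 200 deaths, level shares 5/35/35/25% (10, 70, 70 and 50 deaths) and log hazards 0, 0, 0.30, 0.45. Levels 1 and 2 have the same true hazard. For level 4:
- against level 1: SE = sqrt(1/10 + 1/50) = 0.346, expected z = 0.45/0.346 = 1.30;
- against level 2: SE = sqrt(1/70 + 1/50) = 0.185, expected z = 0.45/0.185 = 2.43.

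The effect is the same, but the expected z lies below 1.96 with one reference and above it with the other.

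**Step 3: kept by AIC and called important (any coefficient p < 0.05).**

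| Setting | Deaths | One reference | Another reference |
|---|---|---|---|
| Shares 5/35/35/25%, log hazards 0/0/0.30/0.45 | 200 | 29% (level 1) | 70% (level 2) |
| same | 800 | 77% | 99.9% |
| same | 1,500 | 96.5% | 100% |
| same | 2,500 | 99.9% | 100% |
| Four equal levels, log HR 0/0.15/0.15/0.30 | 400 | 35% (a middle level) | 52% (an end level) |

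In the first row, among data sets where AIC keeps the factor, the four possible references do not all agree in 70%.

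**Step 4: the joint test in the same settings.**
- First row: b_mean = 0.35 x 0.30 + 0.25 x 0.45 = 0.2175. Noncentrality = 200 x (0.40 x 0.2175^2 + 0.35 x 0.0825^2 + 0.25 x 0.2325^2) = 6.96 on 3 df, giving 59% power for every reference.
- Last row: noncentrality = 100 x (0.15^2 + 0.15^2) = 4.5 on 3 df, giving about 40% for every reference.
- The 5% critical value on 3 df is 7.81, above the AIC threshold of 6, so requiring AIC entry does not lower these figures.

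**Step 5: a factor with no effect.**
- Without selection, any coefficient p < 0.05: 9.0%, 12.5% and 15.6% for 3, 4 and 5 equal levels. With shares 40/35/15/7/3% it is 17.8% (commonest level as reference) or 10.4% (rarest). With unequal four-level shares it ranges from 8.3% to 14.2%.
- Kept by AIC and flagged: about 8.8%, 7.8% and 6.7% for 3, 4 and 5 equal levels, and 4.5% to 9.3% in the unequal settings.
- BIC at n = 350 keeps a null factor in only 0.29%, 0.05% and 0.01% (3, 4, 5 levels), so the flagged rate is far below 5%.
- Joint test: 4.9% to 5.1% in every setting.

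**The case against.** **Coding is inferred.** The article does not say that the Cox model uses indicator terms, and the variables in section 2.2 are data collected, not listed model terms. The singular wording fits binary, continuous or scored terms, where no problem arises. This stands, and it makes the point conditional. It does not remove it, because nominal factors such as pathology cannot be scored and the rule as written has no provision for them.

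**Such detail belongs in the analysis plan.** Reference levels and coding do. But the article does more than omit them: it fixes a decision rule that tests a coefficient, and that rule is unsuitable for multi-category factors.

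**Selection already tests the factor jointly.** If a factor enters as a block, AIC entry does not depend on the reference. The verdict read afterwards still does, as step 3 shows.

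**The contrast is a chosen extreme.** A 5% reference group with 10 of 200 deaths suits only the smaller cohorts. This stands in part: the contrast nearly vanishes by 2,500 deaths. It is still 77% against 99.9% at 800, and it appears with equal level sizes at 400.

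**A stronger reading.** A reader might infer that the rule breaks a stated 5% error rate. The article states no per-factor or familywise error rate; 0.05 is only a cut-off. The 9% to 18% seen in most settings without selection also leaves out the AIC/BIC step. After AIC the rate is about 4.5% to 9%, and lower under BIC, so marked inflation is not shown for the procedure as written.

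**Conclusion.** The point holds in a limited form. For a factor with three or more categories entered as indicators, the stated rule does not test the factor, and its verdict depends on the reference level even after AIC has kept it. The size is material in small and moderate cohorts (29% against 70% at 200 deaths; 35% against 52% with four equal levels at 400) and negligible in the largest. False-positive inflation is secondary.

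The figures rest on indicator coding, on reading the rule as any coefficient below 0.05, on block entry by AIC, and on assumed level shares, effects and deaths. Severity is minor to moderate: a cheap improvement. The list of important factors is one output of section 2.5 among several, so nothing here threatens the study as a whole.

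**What to change.** Replace the coefficient rule in section 2.5 by a factor rule:
- judge each factor in the chosen model by one joint likelihood-ratio or Wald test on k-1 degrees of freedom at 0.05 (for a one-coefficient factor this is essentially the present rule);
- fix the reference level of each multi-category factor in advance, the same across sub-projects where the factor is shared;
- report all level-specific hazard ratios with 95% CIs, in place of a single hazard ratio per factor.

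This costs a sentence or two of text, and the joint test is standard software output. The downside is that in some settings slightly fewer multi-category factors will be declared important. In the 200-death example the joint test gives 59%, below the 70% of the favourable reference but well above the 29% of the unfavourable one.

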## Figures and Tables

**Figure 1 healthcare-10-02146-f001:**
[figure not shown]
Data collection overview.

**Table 1 healthcare-10-02146-t001:** Inclusion and exclusion criteria.

Inclusion Criteria
Patients with pathologically or radiologically diagnosed cancer Age ≥20 years Receiving centrally registered systemic therapy at DPC hospitals within the Tokushukai Medical Group from 1 April 2010 to 31 March 2020
Exclusion criteria
Patients who chose to opt out Simultaneous and metachronous double cancer with disease-free interval of ≤5 years, except for carcinoma in situ/intramucosal cancer cured by local treatment or endoscopic lesions diagnosed as carcinoma in situ Inadequate data extraction (e.g., missing details on past cancer treatment at other hospitals or individual patient data)

**Table 2 healthcare-10-02146-t002:** Laboratory test information.

Blood cell counts	White blood cell (WBC), red blood cell (RBC), hemoglobin (Hb), platelet (PLT), leukocyte fraction, lymphocyte (Lym), neutrophil (Neu), monocyte (Mono), eosinophil (Eo), and basophil (Baso)
Biochemical tests	Sodium (Na), potassium (K), chloride (Cl), calcium (Ca), inorganic phosphorus (IP), magnesium (Mg), aspartate aminotransferase (AST), alanine aminotransferase (ALT), lactate dehydrogenase (LDH), alkaline phosphatase (ALP), γ-glutamyl transpeptidase (GGT), total bilirubin (T-Bil), direct bilirubin (D-Bil), blood urea nitrogen (BUN), creatinine (CRE), uric acid (UA), total protein (TP), albumin (Alb), blood glucose (Glu), hemoglobin A1c (HbA1c), total cholesterol (TC), HDL cholesterol, triglyceride (TG), C-reactive protein (CRP), iron (Fe), and ferritin
Tumor markers	Squamous cell carcinoma-related antigen (SCC), cytokeratin 19 fragment (SYFRA), carcinoembryonic antigen (CEA), carbohydrate antigen 19-9 (CA19-9), carbohydrate antigen 15-3 (CA15-3), carbohydrate antigen 125 (CA125), neuron-specific enolase (NSE), pro-gastrin-releasing peptide (ProGRP), and prostate specific antigen (PSA)
Coagulation/fibrinogenic tests	Activated partial thromboplastin time (APTT), prothrombin time (PT), fibrinogen (Fib), fibrin/fibrinogen degradation product (FDP), and D-dimer
Infectious disease markers	Hepatitis B surface (HBs) antigen, HBs antibody, HB core antibody, HBe antigen, HBe antibody, HB virus DNA quantification, HC virus antibody, syphilis, and HIV
Urinalysis parameters	Urine protein qualitative, urine sugar qualitative

**Table 3 healthcare-10-02146-t003:** Sample size of each cancer type.

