Biliary tract cancer	800
Breast cancer	10,000
Colorectal cancer	10,000
Esophageal cancer	1000
Gastric cancer	5000
Gastrointestinal stromal tumor	500
Kidney cancer	350
Liver cancer	500
Lung cancer	10,000
Ovarian cancer	1500
Prostate cancer	5000
Pancreatic cancer	2500
Uterine body cancer	350
Uterine cervix cancer	350
Urothelial cancer	1000

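### Section 2.5 labels factors important by p<0.05 in a model chosen on the same data and ties the 95% CI to that label, which distorts weak-to-moderate effects in the small cohorts

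*Protocol article*

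**What the plan says.** Section 2.5 of the protocol article sets out a sequence:

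- Univariate step: "Several univariate logistic regression analyses will be performed, with the presence or absence of events in each stratum as the objective variable". The article gives these regressions no stated role in choosing the multivariable model.
- Candidate models: "A hierarchical set of predictive models will be constructed by combining explanatory variables that are expected to contribute". The number of candidate variables is not given.
- Selection: "the Akaike information criterion (AIC) and Bayesian information criterion (BIC) will be used to explore the optimal model".
- Labelling and interval: the rule starts "Regarding the estimated value of the regression coefficient of the explanatory variable included in the optimal model" and continues that, if the p-value is below 0.05, "it will be judged as an important prognostic factor, and the 95% confidence interval of the hazard ratio regarding the magnitude of the contribution" is to be calculated. The interval belongs to the same conditional sentence and refers to the factor just labelled.

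The same rule serves all cancer types in Table 3, whose expected sizes run from 350 (for example "Kidney cancer") to 10,000.

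**The concern.** The data that choose the model also test its coefficients, as if the model had been fixed beforehand. A second filter follows: only factors with p<0.05 get the label and, read literally, an interval. An estimate that must pass a significance filter before it is shown is on average too far from the null, and its interval misses the truth too often when the true effect is small relative to its standard error.

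This is a rule that the article states, not a detail left to another document. Prognostic factors for overall survival are a declared aim (Introduction), and the Discussion directs the results to guidelines and treatment decisions. In the smaller cohorts a reader would see inflated HRs with intervals that look conventional, and no intervals for the other covariates in the same model.

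**Working it through.** **Inputs from the article.** p<0.05 (taken as two-sided, |z|>1.96, to match the 95% CI); AIC and BIC; Table 3 sizes. Table 3 sums to 48,850, which reproduces the total in the Abstract. Eight of its 15 cancer types have 350 to 1,000 patients: 800 + 1,000 + 500 + 350 + 500 + 350 + 350 + 1,000 = 4,850, or 9.9% of the total. Breast, colorectal and lung together have 30,000.

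**Assumptions, not in the article.** 60% of patients die (70% as a check); a balanced binary factor; log HR approximately normal with SE = 2/√deaths.

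**1. Coverage and exaggeration when results are shown only if p<0.05.** Let δ = true log HR / SE.

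- P(p<0.05) = Φ(δ − 1.96) + Φ(−1.96 − δ). At δ = 1 this is 0.170.
- At δ = 1 the interval covers when z lies between −0.96 and 2.96. Together with z > 1.96 the probability is Φ(1.96) − Φ(0.96) = 0.9750 − 0.8315 = 0.1435. Coverage = 0.1435/0.170 = **84%**.
- Mean |z| given p<0.05 at δ = 1 is 2.49, so the log HR is exaggerated about **2.5-fold** in absolute size.
- At δ = 0.5, P(p<0.05) = 0.079, coverage is 60% and exaggeration 4.8-fold.
- For a null factor, coverage among reported intervals is 0% by construction.

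With 350 patients there are 0.60 × 350 = 210 deaths and SE = 2/√210 = 0.138. So δ = 1 is HR exp(0.138) = 1.15, and δ = 0.5 is HR 1.07.

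**2. The same formulas across cohort sizes (60% deaths).**

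| Patients (deaths) | True HR | Coverage if p<0.05 | Log HR exaggeration |
|---|---|---|---|
| 350 (210) | 1.1 | 73% | 3.5-fold |
| 350 (210) | 1.2 | 90% | 1.9-fold |
| 350 (210) | 1.3 | 95% | 1.4-fold |
| 350 (210) | 1.5 | 97% | 1.1-fold |
| 1,000 (600) | 1.1 | 88% | 2.2-fold |
| 1,000 (600) | 1.2 | 96% | 1.3-fold |
| 10,000 (6,000) | 1.1 | 97% | 1.03-fold |

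At 70% deaths, coverage for HR 1.1 is 75% at 350 patients and 89% at 1,000, so the death rate matters little.

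**3. What the selection step adds.**

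- AIC keeps a one-parameter term when z² > 2, that is p<0.157. A null term that AIC has kept therefore has p<0.05 with probability 0.05/0.157 = **32%**.
- Per candidate, however, the false-label rate after AIC stays at 5% for independent candidates and was 5.4% to 6.3% for correlated ones (simulation with 20 candidates, 15 of them null, backward elimination, 70% deaths).
- In that simulation AIC then p<0.05 labelled at least one null factor in 53% to 63% of analyses. Testing 15 independent null factors with no selection gives 1 − 0.95^15 = 54%. Most of the false labels are multiplicity.
- BIC keeps a term when z² > ln n, that is p<0.0155 at n = 350 and p<0.0024 at n = 10,000. In the same simulation it labelled at least one null factor in 24% to 47% of analyses at n = 350 and in about 4% at n = 10,000.

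**4. What the label means by cohort.** Smallest HR reaching p<0.05 = exp(1.96 × 2/√deaths): **1.31** with 210 deaths (350 patients) and **1.05** with 6,000 deaths (10,000 patients).

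**The case against.** The strongest reply is about scale and scope.

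- *Many false factors.* A reader might take the 61 laboratory items in Table 2 (for example "Activated partial thromboplastin time (APTT), prothrombin time (PT), fibrinogen (Fib), fibrin/fibrinogen degradation product (FDP), and D-dimer") as candidates and infer that about four false factors per small cohort follow from AIC selection. The article does not support this. Table 2 lists data to be extracted, not model covariates; backward elimination is not stated; and a fixed model with 61 null covariates and no selection already gives 61 × 0.05 = 3.05 false labels. AIC raises that to about 4, and BIC lowers it to about 1. This objection stands.
- *Redundant under BIC.* A reader might infer that the p<0.05 rule screens nothing once BIC has been applied. That holds only if every single-term deletion is compared. With a hierarchical or blockwise set of models, a retained model can contain terms with p>0.05. This objection stands too.
- *Inflation everywhere.* The bias is negligible for real effects in the three largest cohorts, and for HR 1.5 at 350 patients it is about 1.1-fold. This stands.
- *Exploratory work.* The article speaks of exploring for the model, and the sample sizes rest on no hypotheses. This stands only in part: the next sentence is a yes/no rule, and its results are meant for guidelines.
- *Intervals for all.* The sentence might be meant loosely. As worded, the interval belongs to the factor judged important; if all were intended, the text needs correcting anyway.
- *Condensed article.* Penalised models, a single criterion and false-discovery-rate control are matters of preference or of a later plan, and their absence is no fault here.

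**Conclusion.** The point holds in a limited form. Followed as written, the rule gives intervals below 95% coverage and exaggerated HRs for weak-to-moderate effects in cohorts of 350 to about 1,000 patients: 84% and about 2.5-fold at a true effect of one SE. It does little harm to real factors with HR of 1.1 or more at 10,000 patients. The 32% figure is conditional on a null term having been kept by AIC; how many false labels arise depends mainly on a candidate count that the article does not give. The label is not comparable across cancer types, because the HR needed to earn it runs from about 1.31 down to 1.05. Kaplan–Meier estimates of overall survival are unaffected.

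The figures rest on a normal approximation, a balanced binary factor and 60% deaths. Other values change the size but not the direction. This should be fixed; it is not a reason to hold the study.

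**What to change.** Change Section 2.5, or the analysis plan of each sub-project, as follows:

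1. Report the HR and 95% CI for every covariate in the final model, whatever its p-value. This removes the p<0.05 filter but not the AIC/BIC filter, so the second step is also needed.
2. Bootstrap the whole selection procedure within each sub-project, and report selection frequencies and optimism-corrected performance. Describe the p<0.05 label as exploratory and judge importance on the HR and its CI.

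No new data are needed. The cost is a few sentences and some computing time. The downside is wider intervals and fewer factors called important.
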